#### Non-specific clinical outcomes

We will estimate VE for non-specific clinical outcomes: primary care consultations for ILI; all-cause emergency hospitalisation and death; and emergency hospitalisation and death due to influenza/pneumonia. Hospital admissions and consultations can have multiple events and each event will be counted.

For this proposal we have adopted methods we found in previous studies to be optimal for measuring VE and accounting for bias and confounding.^47^ Adjusted rate ratios of VE for prevention of hospitalisation/death/general practice consultation will be derived from time-dependent Cox models, taking into account the time at risk and the possibility of multiple events (not for death). Models will include a cluster term to account for intrapractice correlation. These models will adjust for gender, age, deprivation and clinical risk group and exposure to vaccination in each season included as a time-dependent covariate. Each season, individuals will begin in the unvaccinated group (and will accumulate time at risk) until 14 days after the receipt of the vaccine; then they will switch to the vaccinated group.

In all models used to estimate the VE, we will adjust for variables associated with the receipt of a vaccination and effect modifiers, such as vaccinations, consultations and hospitalisation in the previous influenza season, SIMD, urban/rural status, smoking status, Charlson score and pregnancy.

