## Methods

### Study design and population

Vaccine uptake will be reported using serial cross-sectional surveys of each influenza season. The test-negative design (TND)^19^ will be used to measure VE for the RT-PCR outcomes and a cohort study design for non-specific clinical outcomes, for example, hospitalisation or death from influenza or pneumonia.

We will seek to extract data on up to 1.25 million people in Scotland by recruiting 220 general practices into our study. Each patient will contribute person-time to each influenza season while alive and registered with a participating general practice.

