### Exposure definition

For people in at-risk groups, influenza vaccinations (Trivalent Influenza Vaccine (TIV) and LAIV for preschool children aged ≥2 years) are free and administered by general practice.^29^ Data on influenza vaccination carried out in general practice (including CHI and date of administration) are recorded to enable reimbursement. Information on individuals receiving LAIV in schools is collated in the SIRS database and will be extracted for this analysis.^21^ Vaccination will be used to define exposure status if it is given at a time point between 1 September and the end of the influenza season (figure 1). An individual will be defined as vaccinated 14 days after the seasonal influenza vaccine has been administered.^30^ The time period from the first day of the influenza season to day 14 postvaccination will be defined as ‘unexposed’ and the period from day 14 postvaccination until the end of the influenza season will be defined as ‘exposed’. Therefore, those vaccinated between the start of the preinfluenza period up until 14 days before the influenza season will be defined as ‘exposed’ for the duration of the influenza season. We will exclude participants vaccinated <14 days prior to the RT-PCR test as a sensitivity analysis.

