### Vaccine effectiveness

#### RT-PCR outcomes

For VE using information from linked virological RT-PCR swab data (a binary event) we will carry out a nested case test-negative control study.^19^ Influenza positivity will be compared with no influenza among patients who have ILI symptoms and tested for influenza. The primary analysis will be through a logistic generalised additive model where the effects of gender, age, socioeconomic status (SIMD^33^) and being in an at-risk morbidity group are adjusted for (a TND study). A spline function for time during each season will be included to model the background rate of influenza and correct for any potential bias associated with the proportions of test-negative and test-positive patients at different periods. VE will be measured by comparing the results from swabs taken after vaccination among those vaccinated to swabs taken among those unvaccinated at the time the swab is collected. Vaccination will be used to define exposure status if it was given at a time point between the 1 September and the end of the influenza season (figure 1). The adjusted estimate of VE=(1**−**OR)×100, where the OR is derived from the coefficient of vaccine status in the model. In our main analysis, we will assess only the first dose when two doses are given. We will carry out analysis stratified by influenza A (H1—including pandemic influenza and H3 subtype where recorded) and B.

We will carry out a number of sensitivity analyses for the primary end point:
*Non-sentinel* versus *sentinel*: We will explore the validity of using laboratory-confirmed influenza tests from non-sentinel primary care and secondary care sources versus sentinel primary care practices. Patient characteristics of individuals swabbed in non-sentinel primary care practices and secondary care will be described and any interaction between source of swab and outcome will be tested.*Negative controls*: As there should be no VE for influenza vaccine for these outcomes, we will explore the use of laboratory-confirmed infections (currently 10 respiratory viruses including rhinovirus and adenovirus) tested using multiplex RT-PCR at the same time as the influenza RT-PCR.*LAIV VE in younger/immunodeficient*: For younger vaccine-naïve or immunodeficient children receiving LAIV, we will account for any second dose in our model.

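### Secondary-outcome Cox models: with age and risk group only as adjustment terms under a common baseline, differing seasonal patterns can be read as vaccine effect while uptake is still rising

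*Protocol article*

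**What the plan says.** The section on non-specific clinical outcomes (under Vaccine effectiveness) covers ILI consultations and "all-cause emergency hospitalisation and death; and emergency hospitalisation and death due to influenza/pneumonia". Adjusted rate ratios "will be derived from time-dependent Cox models, taking into account the time at risk and the possibility of multiple events (not for death"). On covariates: "These models will adjust for gender, age, deprivation and clinical risk group and exposure to vaccination in each season included as a time-dependent covariate". The only other structural term is for practice: "Models will include a cluster term to account for intrapractice correlation". The section then lists further adjustment variables, such as previous vaccination and healthcare use, smoking and Charlson score. None of these lets the seasonal pattern differ by age.

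On the population, Study design and population states: "Each patient will contribute person-time to each influenza season while alive and registered with a participating general practice".

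On exposure time, two sections differ. The Cox section says: "Each season, individuals will begin in the unvaccinated group (and will accumulate time at risk) until 14 days after the receipt of the vaccine", after which they switch to the vaccinated group. Exposure definition says: "The time period from the first day of the influenza season to day 14 postvaccination will be defined as" unexposed, and it treats anyone vaccinated at least 14 days before the season as exposed for the whole season.

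**The concern.** In a Cox model with a common baseline, one curve describes how the hazard moves over the season, and age and risk group only scale it up or down. People outside the target groups are nearly all unvaccinated. They supply almost no vaccinated-versus-unvaccinated contrast, but as the majority they largely set the shape of the curve.

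People aged 65+ and at-risk people change from unvaccinated to vaccinated during autumn. If their winter rise differs in height or timing from that of everyone else, vaccination is the model term that changes within their follow-up, so it absorbs part of the mismatch.

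At stake is a VE for ILI, admission or death that is shifted in either direction. A large cohort would make it look precise. Pooling seasons would narrow the interval without removing a shift that recurs each year.

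**Working it through.** The article gives no event counts, hazard ratios or power for the Cox analysis, so there is no stated figure to reproduce. The check is of the mechanism.

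**1. When can bias arise?** With weekly ties, the Cox model is equivalent to a Poisson model with week terms and a person-time offset. Let O(g,t) be the expected events in group g and week t, E(g,t) the fitted events under week + group terms, and p(g,t) the vaccinated share. With a true HR of 1, the score for the vaccine term at HR 1 is

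S = Σ_g Σ_t p(g,t) × [O(g,t) − E(g,t)].

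The group terms force Σ_t [O − E] = 0 in each group, and the week terms force Σ_g [O − E] = 0 in each week. It follows that:
- if all groups share one seasonal shape, O = E and S = 0;
- if uptake is constant over the risk window, p(g,t) = p(g) and S = Σ_g p(g) × 0 = 0;
- if the baseline is stratified by group, E = O and S = 0;
- if shapes differ and uptake changes by different amounts in different groups, S is in general not 0.

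Both conditions are needed: different seasonal shapes, and uptake changing during the time at risk.

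**2. Inputs for the size.**
- From Sample size: 1.25 million people; 18% aged 65+; 70% uptake at 65+; 40% uptake in asthma, used as a proxy for under-65 at-risk.
- Assumed, not in the documents: 15% under 65 and at risk; 67% never offered vaccine (100 − 18 − 15), with 1% uptake; uptake centred on week 8 after 1 September; winter peaks of relative height 0.5 to 6 around weeks 20 to 22.

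**3. Results with a common baseline** (VE = 1 − HR):

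| Follow-up | Fitted HR, true HR 1.0 | Apparent VE | Fitted HR, true HR 0.7 | Apparent VE (true 30%) |
|---|---|---|---|---|
| 1 September to 31 May | 0.922 to 1.071 | +7.8% to −7.1% | 0.640 to 0.754 | 36.0% to 24.6% |
| Weeks 6–29 (overlaps campaign) | 0.960 to 1.029 | +4.0% to −2.9% | 0.668 to 0.723 | 33.2% to 27.7% |
| Weeks 14–29 (uptake level) | 1.000 | 0 | 0.700 | 30% |

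Over the full period with true HR 1.0, a mild difference in peak height gives HR 0.993, a two-week shift in peak gives 1.013, and identical shapes give 1.000. The sign follows the assumption: larger winter peaks in younger people push the HR below 1, and larger peaks at 65+ push it above 1. A second set of assumed curves gave HR 0.93 to 1.08 from 1 September, 0.95 to 1.06 with overlap, and essentially 1.00 after uptake levelled off.

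**4. Remedies** (1 September to 31 May):
- Baseline stratified by group: 1.000 when the truth is 1.0, and 0.700 when it is 0.7, in every scenario.
- Never-offered people excluded but one baseline kept: 0.969 to 1.018 (VE +3.1% to −1.8%) when the truth is 1.0, and 0.674 to 0.715 when it is 0.7. The bias is smaller but still present.

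**5. Precision.** With an assumed 20,000 or so events, stratifying moves the standard error of log HR from 0.0238 to 0.0248, and 0.0248 / 0.0238 = 1.04. Across the scenarios tried, the increase was at most about 5%. For scale, a fitted HR of 0.94 lies |ln 0.94| / 0.024 = 0.062 / 0.024 = 2.6 standard errors from 1.

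**The case against.** The strongest reply is that the text says only that the models adjust for age and risk group. It does not say there is one baseline, and an article may leave strata and time axis to the full plan. The objectives ask for VE in at-risk groups, Study period limits the children's analysis to the ages being offered LAIV, and the section on annual and pooled analyses foresees subgroups. Group-specific fits are therefore compatible with the plan. This stands, and it is why the point rests on the natural reading of the Cox section rather than on an explicit statement. But that section names a model and its terms and does not carry those restrictions over.

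Second, the bias is conditional. If time at risk is the influenza season alone and vaccination is essentially complete by then, it vanishes. This also stands. The article does not secure that case: the Cox section starts everyone unvaccinated, and season dates come from surveillance, so an early season can overlap the campaign.

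Third, the curves are assumed and the range changes sign. The exact recovery after stratification is partly built in, because each group was given one uniform shape. Both are fair. Differences within a stratum would remain, so the age bands need to be reasonably fine.

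A reader might infer more than the documents support in two ways. One is that the clock is fixed at 1 September: the Cox section names no date, and Exposure definition counts from the first day of the influenza season. The other is that the test-negative analysis has the same fault, since it too names no eligibility limit ("Influenza positivity will be compared with no influenza among patients who have ILI symptoms and tested for influenza"). That model is logistic, has no Cox baseline and already carries a spline for time in season. A common at-risk effect across ages there would be a separate question, not supported by this check.

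**Conclusion.** The point holds for the secondary non-specific outcomes, in conditional form. On the natural reading, age and clinical risk group are adjustment terms under a common baseline across all registered patients. Differing seasonal patterns then enter the vaccine effect whenever uptake is rising during the time at risk.

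Taking both sets of assumed curves together, a null vaccine reads as a VE of roughly −8% to +8% from 1 September, a few percent with overlap, and about 0 after uptake has levelled off. These figures rest on assumed curves, campaign timing and group shares. They show that the bias can matter, not that any particular bias will occur. The change is worth making before the models are fitted, because it is cheap and removes the dependence on an untested assumption.

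**What to change.** 1. Stratify the Cox baseline hazard by age band and clinical risk group, or fit the models separately within each target group (children in the LAIV programme that season, under 65 at risk, 65+). Restricting to eligible people while keeping one baseline is not enough.
2. State the time axis and the risk window. Reconcile the Cox section, where everyone begins each season unvaccinated, with Exposure definition, where earlier vaccinees are exposed for the whole season.
3. State which people enter the Cox models each season.

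The cost is a change in model specification and a standard error up to about 5% larger. No new data are needed.

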### Sample size

We expect a final total sample size of up to 1.25 million from 220 practices. Using data from the PIPER 2014/2015 cohort, which has 263 000 individuals, 16% are aged 2–17, and 18% aged 65+.^48^ Vaccine uptake among children aged 3–12 years is 60% and vaccine uptake among those aged 65+ is 70%. Linked to this cohort from all virology tests in Scotland were 1745 RT-PCR tests overall; 331 RT-PCR tests among 2–17 years old; 366 RT-PCR tests among those aged 65+. This gives a multiplier ratio of around 5:1 from the PIPER cohort to the SIVE II cohort and this is used to estimate the numbers of RT-PCR tests expected each year. We expect 1800 RT-PCR tests per year among those aged 65+, 1650 laboratory tests per year among those aged 2–17. We expect 1745/12×5=630 patients with asthma swabbed per year as about 12% of the population is treated for asthma.

Using data generated from the SIVE project,^49^ we estimate a vaccination rate of 60% among children targeted for receipt of LAIV and a swab positivity rate of 20% among the unvaccinated. This should give 90% power to detect a VE of 31% based on 1650 swabs in one season. Pooling data over two seasons give an estimated 3300 swabs in children eligible for vaccination and a 90% power to detect a VE of 22%.

For 65+ year olds targeted for receipt of TIV where there is a vaccination rate of 70% and a swab positivity rate of 10% among the unvaccinated we anticipate an 80% power to detect a VE of 39% where we estimate that there will be 1800 swabs each year in the later years. During the peak influenza activity when swab positivity might increase to 20% there is a 90% power to detect a VE of 31%. About 1 in 12 of the population is treated for asthma^50^ and we anticipate 1260 swabs among patients with asthma in final two seasons. Assuming 40% are vaccinated and that the swab positivity is around 15% gives 80% power for a VE of 35%. For an influenza type/subtype which has 50% of the total cases, then the detectable VEs will be 40–50% with 90% power. For a type/subtype which has about 25% of the cases, then the detectable VEs will increase to over 60% with 90% power. These powers above do not take into account design effects for the clustering of patients within GP practices. Analyses of the historic PIPER cohorts^48^ has revealed design effect of <7% and this serves to increase the detectable VE by about two percentage points.

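### The asthma swab count does not follow from its own equation or from either stated prevalence, so the 1260 swabs behind the asthma power figure are unsupported; the error is minor and runs low

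*Protocol article*

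**What the plan says.** All of this stands in the Sample size section of the protocol article. Expected swab numbers are scaled up from a 2014/2015 surveillance cohort of 263 000 people: "Linked to this cohort from all virology tests in Scotland were 1745 RT-PCR tests overall". The scaling factor is given as follows: "This gives a multiplier ratio of around 5:1 from the PIPER cohort to the SIVE II cohort".

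For asthma the section then writes: "We expect 1745/12×5=630 patients with asthma swabbed per year as about 12% of the population is treated for asthma". Further on it gives the prevalence again in a different form, "About 1 in 12 of the population is treated for asthma", and carries the count forward over two seasons: "we anticipate 1260 swabs among patients with asthma in final two seasons". The power statement rests on that number: "Assuming 40% are vaccinated and that the swab positivity is around 15% gives 80% power for a VE of 35" per cent.

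**The concern.** One sentence contains two faults. The equation is false, and the reason attached to it (12%) is not the operation performed (division by 12, that is, 8.3%). The later sentence repeats the prevalence as one in 12. Both sentences describe the share of the population treated for asthma, so they cannot be read as two different definitions.

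The wrong result is then used: 2 × 630 = 1260, the number on which the asthma power figure depends. People with asthma are named in the second study objective, and the Introduction criticises earlier work as underpowered in such subgroups. A reader should therefore be able to trace the asthma figure to its inputs. As written, they cannot tell whether the investigators expect about 630, 730 or 1050 asthma swabs a year.

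**Working it through.** **Inputs** (Sample size section unless noted): 1745 tests in the source cohort; multiplier 5; asthma share 12% or 1 in 12; 40% vaccinated; 15% positivity; VE 35%; two-sided 5% test (Statistical analysis section).

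**Step 1: the yearly count**
- As printed: 1745 / 12 × 5 = 727. The stated 630 is 13% lower (630 / 727 = 0.87).
- With 12%: 1745 × 0.12 × 5 = 1047. The stated 630 is 40% lower (630 / 1047 = 0.60).
- Share implied by 630: 630 / (1745 × 5) = 630 / 8725 = 7.2%.

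**Step 2: could rounding explain it?** The unrounded multiplier is 1 250 000 / 263 000 = 4.75. It gives 691 (1 in 12) or 995 (12%), neither of which is 630. The other groups do follow from the multiplier, using "331 RT-PCR tests among 2–17 years old; 366 RT-PCR tests among those aged 65" and over: 331 × 5 = 1655 (stated 1650) and 366 × 5 = 1830 (stated 1800). Only the asthma count fails.

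**Step 3: the article's power figure, taking 1260 as given.** I used a two-proportion test with pooled variance under the null, 15% as positivity in the unvaccinated, and VE as 1 − RR.
- Unvaccinated n0 = 0.6 × 1260 = 756; vaccinated n1 = 0.4 × 1260 = 504.
- p0 = 0.15; p1 = 0.15 × (1 − 0.35) = 0.0975; difference 0.0525.
- Pooled p = 0.6 × 0.15 + 0.4 × 0.0975 = 0.129.
- Null SE = √[0.129 × 0.871 × (1/756 + 1/504)] = 0.01928.
- Alternative SE = √[0.15 × 0.85 / 756 + 0.0975 × 0.9025 / 504] = 0.01853.
- z = (0.0525 − 1.96 × 0.01928) / 0.01853 = 0.79, so power is 78.7%.

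This is close to the stated 80%. Solving for 80% power gives a detectable VE of 35.5%, against 35% stated.

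**Step 4: the same calculation with the corrected counts**

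| Basis | Per year | Two seasons | Power for VE 35% | VE detectable with 80% power |
|---|---|---|---|---|
| As stated | 630 | 1260 | 78.7% | 35.5% |
| 1 in 12 | 727 | 1454 | 84.3% | 33.3% |
| 12% | 1047 | 2094 | 94.7% | 28.1% |

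**The case against.** The strongest reply is that nothing depends on the slip. The study uses routinely collected records, no design decision is shown to rest on the asthma count, and pooling over seasons is already allowed for subgroups. Either stated prevalence gives more swabs than claimed, so the planned 80% power is met in both cases. If 1 in 12 is right, the detectable VE moves by about two percentage points, roughly the allowance the section already makes for clustering. All of this stands, and it limits the weight of the point. It does not make the equation true or show which prevalence was meant.

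A second reply is that 630 was reached another way. Taking 12% of the tests outside the two named age groups gives (1745 − 331 − 366) × 0.12 × 5 = 629. But the article describes no such step, it is not the printed formula, and it would leave out asthma swabs at ages 2–17 and 65+, whereas the 1260 carries no age limit. If this was the method, the text still needs correcting.

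Nor is it a one-character misprint. Changing 630 to 727 leaves the 12% in conflict with the divisor. Changing the divisor to a 12% share leaves 630 wrong.

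A reader might infer that the asthma analysis is underpowered, or that the power calculation is itself wrong. The article supports neither inference: the count errs low, and the power figure approximately reproduces once 1260 is accepted. A reader might also take the 40% understatement as established. It holds only if 12% is the intended prevalence; the printed division and the later sentence both point to 1 in 12, where the gap is 13% (about 9% with the unrounded multiplier, 630 / 691 = 0.91).

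**Conclusion.** The point holds as a minor planning error. The yearly count of 630 is wrong as written, the two prevalences contradict each other, and the two-season 1260 therefore has no stated basis. The true product of the printed expression is 727. The count is understated by 13% (1 in 12) or 40% (12%), and power for a VE of 35% would be about 84% or 95% instead of the stated 80%.

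These results assume the article's multiplier of 5, its premise that asthma patients' share of swabs equals their share of the population, 15% positivity in the unvaccinated, and VE as 1 − RR. I used the risk-ratio scale because it comes close to the article's own figure. The analysis defines VE as 1 − OR. That difference affects all the power figures, is not part of this error, and should be raised separately.

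**What to change.** In the Sample size section, state one asthma prevalence, checked against the source cited there, and use it in both sentences. Correct the equation to match. Then restate the three dependent numbers:
- if 1 in 12: 727 per year, 1454 over two seasons, VE of about 33% detectable with 80% power;
- if 12%: 1745 × 0.12 × 5 = 1047 per year, 2094 over two seasons, about 28%.

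If 630 came from a different calculation, print that calculation and the population it covers. The cost is a few lines of text; design, data extraction and analysis are unchanged.

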### Statistical analysis

Baseline characteristics will be summarised by vaccination status for the whole cohort using mean, median or proportion where appropriate together with a measure of dispersion. We will evaluate the baseline characteristics of those tested and not tested using RT-PCR. Missing data will be reported for each variable. A 5% significance level will be used for hypothesis tests for the primary outcome. All p values will be two sided. All analyses will be undertaken in R (V.3.2.3; R Core Team (2015). R: A language and environment for statistical computing. R Foundation for Statistical Computing, Vienna, Austria. URL https://www.R-project.org).

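### The five point power statements fit a VE defined as 1 minus the ratio of swab positivities, but the study will report 1 minus the odds ratio, on which power is about 69–80% rather than 80–90%

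*Protocol article*

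**What the plan says.** The RT-PCR outcomes section sets the analysis: "The primary analysis will be through a logistic generalised additive model". VE is one minus the odds ratio, times 100, "where the OR is derived from the coefficient of vaccine status in the model". The Statistical analysis section adds "A 5% significance level will be used for hypothesis tests for the primary outcome" and "All p values will be two sided".

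The Sample size section then makes five specific power statements:

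- Children, one season: "we estimate a vaccination rate of 60% among children targeted for receipt of LAIV and a swab positivity rate of 20% among the unvaccinated", followed by "This should give 90% power to detect a VE of 31% based on 1650 swabs in one season".
- Children, two seasons pooled: 3300 swabs, 90% power for a VE of 22%.
- 65+, 70% vaccinated, 10% positive among the unvaccinated, 1800 swabs: "we anticipate an 80% power to detect a VE of 39" per cent.
- 65+ at peak activity, with positivity up to 20%: 90% power for a VE of 31%.
- Asthma, 1260 swabs over two seasons: "Assuming 40% are vaccinated and that the swab positivity is around 15% gives 80% power for a VE of 35" per cent.

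Two looser sentences on influenza types and subtypes follow. The section says that clustering is left out of these powers. It states neither the power formula nor the scale on which VE is measured.

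**The concern.** With an outcome present in 10–20% of swabs, an odds ratio and a ratio of positivities are not interchangeable. At 20% positivity in the unvaccinated, a positivity ratio of 0.69 is an odds ratio of 0.64, which the study would report as a VE of 36%. A reported VE of 31% (odds ratio 0.69) is a smaller contrast: 20.0% against 14.7% positive, not 20.0% against 13.8%.

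If the powers were worked out on one scale and the results are reported on the other, the study has less power than stated for the VE it will publish. The groups affected are children offered LAIV, people aged 65+ and people with asthma, all of which the objectives name. A non-significant VE in the range 22–39% would be read against a power that the design does not deliver. The decision to pool seasons for precision would also start from too favourable a single-season figure.

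**Working it through.** **Inputs.** Swab numbers, uptake, positivity, VE and power are from the Sample size section; the two-sided 5% level is from Statistical analysis. For 65+ at peak, the 1800 swabs and 70% uptake are carried over from the preceding sentence. For asthma, 15% is taken as positivity among the unvaccinated, which the text does not say.

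**Power formula.** Two-proportion normal approximation with n₀ unvaccinated and n₁ vaccinated swabs, and p̄ the overall positivity:

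power = Φ{ [ (p₀ − p₁) − 1.96·√( p̄(1−p̄)(1/n₀+1/n₁) ) ] / √( p₀(1−p₀)/n₀ + p₁(1−p₁)/n₁ ) }

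Only the vaccinated positivity p₁ differs between the scales:

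- Ratio scale: p₁ = p₀(1 − VE)
- Odds-ratio scale: p₁ = OR·p₀ / (1 − p₀ + OR·p₀), with OR = 1 − VE

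**One scenario in full: children, one season.** n₀ = 660, n₁ = 990, p₀ = 0.20, VE = 31%.

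- Ratio scale: p₁ = 0.20 × 0.69 = 0.138. The standard errors are 0.01855 (null) and 0.01904 (alternative). Then (0.062 − 1.96 × 0.01855)/0.01904 = 1.35, and power is 91.1%. This matches the stated 90%.
- Odds-ratio scale: p₁ = 0.138/(0.80 + 0.138) = 0.1471. The standard errors are 0.01880 and 0.01921. Then (0.0529 − 1.96 × 0.01880)/0.01921 = 0.83, and power is 79.8%.

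**All five scenarios**

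| Scenario | n₀ / n₁ | p₀ | VE | p₁ ratio / OR | Stated power | Power, ratio scale | Power, OR scale |
|---|---|---|---|---|---|---|---|
| Children, 1650 swabs | 660 / 990 | 20% | 31% | 13.8% / 14.7% | 90% | 91.1% | 79.8% |
| Children, 3300 | 1320 / 1980 | 20% | 22% | 15.6% / 16.3% | 90% | 90.1% | 77.0% |
| 65+, 1800 | 540 / 1260 | 10% | 39% | 6.1% / 6.3% | 80% | 81.1% | 75.4% |
| 65+ at peak, 1800 | 540 / 1260 | 20% | 31% | 13.8% / 14.7% | 90% | 90.0% | 78.4% |
| Asthma, 1260 | 756 / 504 | 15% | 35% | 9.8% / 10.3% | 80% | 78.7% | 68.5% |

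The ratio scale is within 2 points of the stated power in every row. The odds-ratio scale is 5 to 13 points low.

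**Solved the other way: VE detectable at the stated power**

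| Scenario | Stated VE | Ratio scale | OR scale |
|---|---|---|---|
| Children, 1650 | 31% | 30.4% | 35% |
| Children, 3300 | 22% | 22.0% | 26% |
| 65+, 10% positive | 39% | 38.5% | 41% |
| 65+, 20% positive | 31% | 31.0% | 36% |
| Asthma | 35% | 35.5% | 39% |

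**Does the choice of formula explain it?** An arcsine calculation also reproduces all five on the ratio scale (91.1, 90.0, 80.2, 89.8 and 79.6%) and misses all five on the odds-ratio scale (79.6, 76.8, 74.1, 77.7 and 69.7%). A Wald test on the log odds ratio, the closest simple analogue of the planned model, gives 80.1, 77.2, 76.5, 79.2 and 67.5%. Unpooled and continuity-corrected versions do not rescue the odds-ratio scale either: with the stated uptake, no two-sided version tried comes within 2 points of any stated power. A one-sided 5% test on the odds-ratio scale gives 87.3, 85.3, 83.6, 86.2 and 79.1%. That fits only asthma, and it contradicts the two-sided rule.

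**Subtype sentences.** On the odds-ratio scale at 90% power, a subtype with half the cases has a detectable VE of about 46% (children, one season) or 47% (65+ at peak), inside the stated 40–50%. With a quarter of the cases it is about 61% in both, which fits the statement of over 60%.

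**The case against.** The strongest reply has four parts.

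- *The scale is inferred.* The Sample size section names no formula, so VE there might have been meant as 1 minus a ratio of positivities. That is true, and the finding should be worded as an inference. It does not remove the inconsistency: the only VE that the article defines for the RT-PCR outcome is the odds-ratio one, and the section does not announce another.
- *The inputs are rough.* Swab numbers come from an approximate multiplier and the positivities are approximate. In detectable VE the shift is about 2 to 5 points, and at 10% positivity only about 2. This bears on how much weight to give the point. But rough inputs affect both scales alike, while the scale mismatch always flatters the power. The section thought a clustering effect of about two points worth reporting, and in four of the five scenarios the scale effect is larger.
- *Nothing in the design depends on it.* This stands. The swab numbers are projected from an existing cohort, not derived from a power target, and pooling over seasons is already allowed. A reader might infer that more swabs are needed or that the VE estimates will be biased. The documents support neither: the estimator, model and test are untouched.
- *Not every power statement is affected.* This also stands. A reader might infer that every power figure in the section is overstated. The two subtype sentences give loose ranges without naming a scenario, and in the two scenarios shown above they agree with the odds-ratio scale.

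**Conclusion.** The point holds for the five specific power statements and no further. They fit VE as 1 minus the ratio of positivities and do not fit the odds-ratio VE that the study will report. On the reported scale, the three statements of 90% become about 77–80%, so the type II error roughly doubles from 10% to 20–23%. The two statements of 80% become about 75% (65+ at 10% positivity) and 69% (asthma). The loss is smallest where positivity is lowest.

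The conclusion rests on three things:

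- The ratio scale is inferred from all five figures matching, not read from the text.
- The calculation is an unadjusted two-group comparison before any design effect, which is how the section describes its own powers with respect to clustering.
- The asthma figure assumes that 15% is the positivity among the unvaccinated. Read as overall positivity, the ratio scale gives 85% and the odds-ratio scale 74%. Neither gives the stated 80%, but the odds-ratio power is still the lower.

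This is an error in the stated operating characteristics, not a threat to the validity of the VE estimates.

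**What to change.** Recompute the five statements with positivity in the vaccinated derived from the odds ratio, p₁ = OR·p₀/(1 − p₀ + OR·p₀), and state the formula and the VE scale in the Sample size section. Then do one of two things, in the order children one season, children two seasons, 65+ at 10%, 65+ at 20%, asthma:

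- keep the powers and restate the detectable VEs as about 35%, 26%, 41%, 36% and 39%; or
- keep the VEs and restate the powers as about 80%, 77%, 75%, 78% and 69%.

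Say also whether the 15% positivity in asthma is among the unvaccinated. The subtype sentences can stay, though naming the scenario behind them would let a reader check them. The cost is a few changed figures that look slightly less favourable; data volume and analysis do not change.
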